### 2.3. Outcomes Measurement

The same outcomes will be included in both studies. All of them will be assessed by a trained physical therapist in all groups the previous week, the following week, and 15 days after the 10 intervention sessions. The procedure is presented in Figure 1.

Every outcome will be measured in the ON state of PD patients, 1 h after taking their dopaminergic medication, to ensure their comfort. Nevertheless, Kings Parkinson’s Disease Pain Scale (KPDPS), CPM and TS will be also measured in OFF state, 30 min before medication intake, to assess the effects of both neuromodulation therapies when dopaminergic medication is not acting.

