##### Neurophysiological Outcomes

The excitability of pain-related pathways will be measured by Transcranial Magnetic Stimulation (TMS) markers. Firstly, single pulse TMS will be performed to acquire resting motor threshold (rMT), motor evoked potentials (MEPs) and cortical silent period (CSP). Magstim Rapid2 device with a figure-of-eight magnetic stimulator coil will be used. For all assessments, the magnetic stimulator coil will be placed firstly on the right and secondly on the left M1 with a 5 min rest interval, and surface electromyogram from the contralateral first dorsal interosseous muscle will be recorded. TMS used amplitudes and EMG recordings will be recorded and stored in a computer for off-line analysis [66]. Stimulation output used to reach the rMT, MEP amplitudes and silent periods duration will be taken as outcomes.

Brain activity will be measured by Electroencephalography (EEG). An actiCHamp amplifier (Brain Vision LLC, Morrisville, NC, USA) will be used to amplify and digitize the EEG data at a sampling frequency of 512 Hz. The EEG data will be stored in a PC running Windows 7 (Microsoft Corporation, Washington, DC, USA). EEG activity will be recorded from 64 positions with active Ag/AgCl scalp electrodes (actiCAP electrodes, Brain Vision LLC, Morrisville, NC, USA). The ground and reference electrodes will be placed on AFz and on FCz, respectively Electroencephalography acquisition will be carried out by NeuroRT Studio software (Mensia Technologies SA, Paris, France). The EEG signal processing procedure will be performed using MATLAB functions (MathWorks Inc., Natick, MA, USA), specifically the EEGLab toolbox. The EEG registers performed will be resting (1 min), while FT task (30 s each hand, beginning with the dominant one), while wrist-extension task (5 min each hand, beginning with the dominant one) and with eyes closed (5 min). The participants will be asked to relax in the resting condition; the investigator will ensure they do not fall asleep, especially in resting and in eyes closed registers. Spectral entropy correlation, coherence and interhemispheric divergence differences among experimental group and controls will be analyzed as outcomes.

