### 2.4. Sample Size Calculation

#### 2.4.1. tDCS-Based Study

The simple size for the tDCS-based study was calculated using G*Power software (version 2.1, Heinrich-Heine-Universität Düsseldorf, Düsseldorf, Germany), taking into consideration the design of two intervention groups and three assessment times. The primary outcome was chosen to be King’s Parkinson’s Disease Pain Scale with an estimated effect size of F = 0.25. An α level of 0.05 and a power of 90% was assumed, with a total sample of 28 subjects estimated. Considering a 15% follow-up loss, we estimated a minimal sample size of 32 patients, with a minimal recruitment of 16 required for each of the intervention groups.

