A multiple linear regression analysis will be performed to estimate the strength of the associations between the rMT, PPT, CPM, TS, psychological and functional variables, and pain. CPM, TS and neurophysiological variables will be used as predictors. The strength of the association will be examined using regression coefficients (B), *p* values and adjusted R2. Standardized beta coefficients will be reported for each predictor variable.

For the EEG entropy analysis non-parametric Kruskal–Wallis (KW) tests will be performed to compare the distributions, Mann–Withney U test to evaluate the difference between the median values for Pre-intervention/Controls, Post-intervention/Controls or Pre/Post intervention, and non-parametric Wilcoxon rank-sum test for Pre/Post intervention, with a significance level of 0.05 and the alternative hypothesis of unequal values. Thus, small *p*-values will suggest significant differences between populations.

The first part of the analysis will consist of comparing the differences between ON state versus OFF state in pain intensity, conditioned pain modulation, and temporal summation, and the second part will investigate the effects of the intervention on these same variables comparing the differences between ON state versus OFF state. For this analysis repetitive measures of ANOVA will be performed followed by post-hoc test with Bonferroni correction using the interaction of group factor x state factor and time factor.

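### Section 2.5 tests the within-patient EEG Pre/Post change with an independent-samples test, named twice, so the stated 0.05 level does not hold and some power is lost

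*Protocol article*

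**What the plan says.** Protocol article, section 2.5 (Data Analyses), EEG paragraph. The plan first names the "Mann–Withney U test to evaluate the difference between the median values for Pre-intervention/Controls, Post-intervention/Controls or Pre/Post intervention". It then adds the "non-parametric Wilcoxon rank-sum test for Pre/Post intervention". Both are to be run "with a significance level of 0.05 and the alternative hypothesis of unequal values", that is, two-sided at 0.05.

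On the data, section 2.3 (Outcomes Measurement) says: "All of them will be assessed by a trained physical therapist in all groups the previous week, the following week, and 15 days after" the sessions. EEG is among these outcomes. It stands under section 2.3.2 (Secondary Outcomes), where the neurophysiological text adds: "Spectral entropy correlation, coherence and interhemispheric divergence differences among experimental group and controls will be analyzed as outcomes".

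Section 2.4.1 sets "a minimal recruitment of 16 required for each of the intervention groups". Section 2.4.2 gives the second trial the same size.

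**The concern.** The Wilcoxon rank-sum test and the Mann-Whitney U test are the same procedure. It treats its two columns of values as coming from different people. For the two comparisons with controls that is correct. For Pre/Post it is not: each patient supplies one value to each column. The paragraph names no paired test for this contrast.

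This is not a detail left to an analysis plan that is not shown. The article positively names a test, and the test does not fit the data.

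When a patient's two values are positively correlated, the rank-sum test keeps the between-patient variation in its reference distribution although that variation cancels in the Pre/Post difference. The p values are then too large, the 0.05 level is not the real level, and a true within-patient change is harder to detect than it need be.

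**Working it through.** **Inputs from the article.** Test: rank-sum/Mann-Whitney for Pre/Post, two-sided 0.05 (section 2.5). Pairing: same patients at each visit (section 2.3). Patients: 16 per arm (section 2.4.1), or 14 per arm if the 28 evaluable patients split equally.

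**Inputs that are assumptions.** The article gives no pre-post correlation ρ and no expected change for EEG. I take ρ = 0.3, 0.5 and 0.7, changes of 0.5 and 0.8 SD, normal values and equal variances.

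**The plan's own figure.** The only figure for this comparison is the 0.05 level. The article states no power for EEG; the 90% in section 2.4.1 is for the King's pain scale. If Pre and Post were independent (ρ = 0), simulation at n = 16 gives a rejection rate of 0.045, so the level is about right in the situation for which the test is built.

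**Size under pairing, by formula.** In large samples, pairing multiplies the null variance of the rank-sum statistic by 1 − ρ_S, where ρ_S = (6/π)·arcsin(ρ/2) for normal data. The true level is then 2·[1 − Φ(1.96/√(1 − ρ_S))].

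- ρ = 0.3: ρ_S = 0.288, √(1 − 0.288) = 0.844, 1.96/0.844 = 2.32, level 0.020.
- ρ = 0.5: ρ_S = 0.483, √(1 − 0.483) = 0.719, 1.96/0.719 = 2.73, level 0.006.
- ρ = 0.7: ρ_S = 0.683, √(1 − 0.683) = 0.563, 1.96/0.563 = 3.48, level 0.0005.

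**Size and power by simulation, n = 16.** Bivariate normal pairs; the main run had 20,000 data sets per cell. Where separate runs differ, the range is shown.

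| ρ | Rank-sum type I error | 0.5 SD: rank-sum vs signed-rank | 0.8 SD: rank-sum vs signed-rank |
|---|---|---|---|
| 0.3 | about 0.02 | 22–23% vs 33–34% | 57% vs 67–71% |
| 0.5 | about 0.01 (0.008 in the main run) | 20% vs 44–45% | 58–59% vs 83–84% |
| 0.7 | 0.001 to 0.002 | 16% vs 65–66% | 60–61% vs 96–97% |

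The signed-rank test keeps a type I error of 0.046 to 0.050. The formula and the simulation agree in direction and order of size; the gap at ρ = 0.7 is what a large-sample formula leaves at n = 16.

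**Relative loss of power** (1 − rank-sum/signed-rank, main run). For 0.5 SD: 1 − 0.219/0.342 = 36%, 1 − 0.195/0.450 = 57% and 1 − 0.165/0.661 = 75% at ρ = 0.3, 0.5 and 0.7. For 0.8 SD: 19%, 30% and 38%.

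**Other sample sizes.** With n = 14, ρ = 0.5 and 0.5 SD, power is 16% against 40%. With both arms pooled (n = 32) and 0.5 SD, it is 47% against 76% at ρ = 0.5 and 48% against 93% at ρ = 0.7. With n = 32, 0.8 SD and ρ = 0.5, it is 93% against 99%.

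**The case against.** **Rank-sum may be a slip for signed-rank.** The sentence lists the Wilcoxon test separately from Mann-Whitney and for Pre/Post alone, which would be redundant unless a paired test was meant. That is plausible. But Pre/Post also stands in the Mann-Whitney list ("Post-intervention/Controls or Pre/Post intervention"). Correcting one word would leave a paired and an unpaired test on the same contrast, with different p values and no rule for choosing. The sentence needs correction on either reading.

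**The contrast is not the randomised one.** Section 2.3.2 frames the EEG outcome as a difference between the experimental group and controls, and Mann-Whitney is valid there. The main variables go through repeated-measures ANOVA, which respects the pairing, and the sample size rests on the King's pain scale. This stands, and it limits the weight of the point.

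**Stronger readings that the article does not support.**

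- A reader might infer that most of the power is lost, or that a real change is usually missed. At one arm's n, more than half is lost only for a moderate change with correlation of about 0.5 or more. At 0.8 SD the rank-sum test still detects the change in 57–61% of runs. At 0.5 SD and correlation 0.5 the signed-rank test itself reaches only 44–45%, so small numbers contribute too.
- A reader might infer a risk of false positives. With positive correlation the error goes the other way.
- A reader might extend the point to the Kruskal-Wallis test and ask for a Friedman test. Section 2.5 does not say which groups enter the Kruskal-Wallis test, so no error is shown there.
- A reader might infer that a null EEG result will be taken as evidence against the cortical mechanism. The article announces no such interpretation.

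**Conclusion.** The point holds in a limited form. Section 2.5 names an independent-samples test, under two names, for a within-patient contrast, and that is wrong as written whatever the EEG data look like. The practical size rests on a pre-post correlation and an effect size that the article does not give. Over correlations of 0.3 to 0.7 with 16 patients in an arm, the real level lies well below the stated 0.05. The cost in power runs from about 10 percentage points at correlation 0.3 to about 50 for a 0.5 SD change at correlation 0.7. Outside normal data with equal variances the figures would shift, but the mismatch between test and design would not. Because EEG is a secondary outcome and the error is conservative under positive correlation, this is a should-fix; no primary conclusion changes.

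**What to change.** In the EEG paragraph of section 2.5:

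1. Replace the rank-sum test by the Wilcoxon signed-rank test on each patient's Post minus Pre difference, and state that it is the only test for Pre/Post.
2. Delete Pre/Post from the Mann-Whitney list.
3. Keep Mann-Whitney for Pre-intervention against controls and Post-intervention against controls, where the patients are different people.

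The cost is one sentence of wording, with no new data, visits or patients. The change should be recorded before the EEG results are seen, so that the choice of test cannot depend on them.

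### The EEG entropy plan tests three contrasts at an unadjusted 0.05, names none as deciding, and includes an arm comparison before treatment but no baseline-adjusted arm comparison

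*Protocol article*

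**What the plan says.** Section 2.5 (Data Analyses) begins the EEG plan with an omnibus test: "For the EEG entropy analysis non-parametric Kruskal–Wallis (KW) tests will be performed to compare the distributions". It then assigns a Mann–Whitney U test to "the difference between the median values for Pre-intervention/Controls, Post-intervention/Controls or Pre/Post intervention", and adds a "non-parametric Wilcoxon rank-sum test for Pre/Post intervention". The level and the reading rule for all of these are "with a significance level of 0.05 and the alternative hypothesis of unequal values. Thus, small *p*-values will suggest significant differences between populations". The section does not say which contrast answers the question, and it does not make the pairwise tests conditional on the Kruskal–Wallis result.

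Section 2.3.2 (Neurophysiological Outcomes) lists the recordings: "The EEG registers performed will be resting (1 min), while FT task (30 s each hand, beginning with the dominant one"), followed by wrist extension with each hand and an eyes-closed recording. That is four conditions, or six recordings if the hands are counted separately. It also states: "Spectral entropy correlation, coherence and interhemispheric divergence differences among experimental group and controls will be analyzed as outcomes".

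Bonferroni correction appears twice in section 2.5: after the 2 × 3 ANOVA of the main variables, and after the ON/OFF ANOVA of pain intensity, conditioned pain modulation and temporal summation. Neither statement covers EEG.

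**The concern.** There are two separate problems.

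**The contrasts do not fit the question.** In a randomised trial, any difference between the arms before treatment is due to chance, so a significance test of it cannot inform on the therapy. The pre/post contrast is within-group, and change within one group mixes treatment with time and repeated measurement. The post-intervention arm comparison is valid under randomisation, but it ignores each patient's baseline. The most direct and usually more precise estimate, the post-treatment arm difference adjusted for the pre-treatment value, is not among the three.

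**Nothing limits the number of chances to find a small p-value.** Three contrasts are joined by 'or', several recordings are available, and each test is read at 0.05.

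What is at stake is the interpretation of mechanism. The Introduction makes neurophysiological evaluation the third part of the main aim and presents EEG entropy connectivity as something not studied before in this setting. With 16 patients per arm, a chance EEG difference could be taken as support for how the therapy works.

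**Working it through.** **Inputs from the protocol article**
- Level per EEG test: 0.05, two-sided (section 2.5).
- Contrasts: 3 (section 2.5).
- Recordings: 4 conditions or 6 recordings (section 2.3.2).
- Patients: 16 per arm (section 2.4).

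**Assumptions not in the documents**
- Entropy is tested separately in each condition or recording, at one post-intervention visit.
- The test statistics share a common correlation ρ of 0, 0.5 or 0.7.
- Each test holds its nominal level.

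**Formula.** For m independent tests with no true effect, P(at least one p < 0.05) = 1 − 0.95^m. With common correlation ρ it is

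1 − ∫ φ(u) [Φ((1.96 − √ρ·u)/√(1−ρ)) − Φ((−1.96 − √ρ·u)/√(1−ρ))]^m du.

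**Starting point.** For m = 1 this returns 5%, the stated level, so 0.05 describes one test only.

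**Results for one trial**

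| Tests counted | m | ρ = 0 | ρ = 0.5 | ρ = 0.7 |
|---|---|---|---|---|
| Post/Controls, 4 conditions | 4 | 18.5% | 15.6% | 13.0% |
| Post/Controls, 6 recordings | 6 | 26.5% | 20.7% | 16.4% |
| Pre/Controls and Post/Controls, 6 recordings | 12 | 46.0% | 31.9% | 23.2% |

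For example, 1 − 0.95^4 = 0.185 and 1 − 0.95^6 = 0.265.

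**Which row matters.** Only Post/Controls results can be read as a difference after treatment. Half of the 12 tests in the last row are baseline comparisons. A false positive there is a chance imbalance, not an EEG change, so that row measures how often some significant arm difference would appear, not how often a treatment effect would be falsely suggested.

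**Pre/Post.** Mann–Whitney and Wilcoxon rank-sum are the same unpaired test, applied here to paired data. In a simulation with 16 patients, its level for one recording was 0.2% to 1.0% (pre-to-post correlation 0.7 and 0.5). Over six recordings it gave at least one false positive in 0.8% to 4.8% of trials. As written, it therefore adds little.

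**Check with rank tests.** Simulated Mann–Whitney tests with 16 per arm (pre-to-post correlation 0.5, 1,000 repetitions) gave at least one false Post/Controls result in 15% to 17% of trials over four conditions and 17% to 23% over six recordings, for correlations of 0 to 0.7 between recordings. This agrees with the table within simulation error.

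**If Kruskal–Wallis were a gate.** Requiring a significant Kruskal–Wallis result in the same recording gave about 9% to 14% for any of the three contrasts, over four to six recordings with correlations of 0.3 to 0.7. That simulation used a paired signed-rank test for Pre/Post, and a Kruskal–Wallis test over active-arm pre, active-arm post and control-arm pre values. The rate is lower, but still above 5%.

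**The case against.** The strongest opposing case has five parts.

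1. **It is not shown that a false EEG finding is likely.** This stands. A reader might infer from the number of tests that a chance finding is more probable than not. The treatment-relevant rows above stay at or below about 26%. Passing 50% requires, for instance, 18 tests (six recordings × three contrasts) treated as independent (60%), which is implausible for recordings from the same patients, or 54 tests (64% at ρ = 0.5) obtained by applying the entropy plan to coherence and interhemispheric divergence as well. Section 2.5 speaks only of entropy.

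2. **The multiplier is assumed.** This also stands in part. Section 2.3.2 lists what is recorded, not that each recording or hand is tested separately. The rates are therefore conditional, and both counts are shown.

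3. **Omnibus-then-pairwise is a natural reading.** It is, but the text does not make one depend on the other, and the gated rate still exceeds 5%.

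4. **'Controls' is undefined in section 2.5.** True. The reading as the randomised control arm rests on section 2.3.2, which speaks of the experimental group and controls, and on a design that has no other control group.

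5. **Secondary-endpoint multiplicity is commonly left to an analysis plan that is not shown.** A missing adjustment alone would not be a finding. Here, however, the article itself fixes the contrasts, the level and the rule for reading small p-values, and one of those contrasts is uninformative by design.

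A reader might also infer that the plan means to read a difference before treatment that is absent afterwards as normalisation. The protocol article contains no such rule, so this cannot be held against it.

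**Conclusion.** The point holds in a limited form. Section 2.5 fixes three EEG entropy contrasts at an unadjusted 0.05 with none deciding. If 'Controls' is the randomised arm, one of them tests the arms before treatment, and none estimates the baseline-adjusted arm difference. If each condition or recording is tested, the stated 5% becomes roughly 13% to 26% per trial for the post-intervention arm comparison, about three to five times the nominal level. The range covers four conditions to six recordings and correlations of 0.7 to 0. A Kruskal–Wallis gate would reduce it.

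EEG is a secondary outcome. The sample size (section 2.4) and the planned comparison of the two approaches (section 2.6) rest on the KPDPS, so no efficacy conclusion is affected. Only the strength of mechanistic claims is. Formal adjustment across every exploratory EEG result would be a matter of preference and is not required by this point.

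**What to change.** In section 2.5, replace the three EEG contrasts with one named comparison: the between-arm difference in post-treatment entropy, adjusted for its pre-treatment value, in one recording and at one visit chosen before the data are seen. The choice of recording is the investigators'. A single named test holds the 5% level.

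Drop the pre-intervention arm comparison as a significance test and show baseline EEG values descriptively by arm. Label all other EEG measures, recordings and contrasts exploratory. State what 'Controls' means.

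The cost is analysis-plan wording only. It needs no new data or patients. The downside is that fewer EEG results can be called significant.

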### 2.5. Data Analyses

The SPSS software package (version 25.00; SPSS inc., Chicago, IL, USA) will be used by a blinded statistician for statistical analysis of the data. Demographic and clinical variables will be presented as mean and standard deviation. A 95% confidence interval (CI) will be taken, considering statistically significant all those values that had a *p* < 0.05. Parametric statistical tests will be used for hypothesis testing (*n* > 30). To show differences in the main variables, an analysis of variance (ANOVA) 2 × 3 of repeated measurements will be carried out taking time and group as factors, being the groups active-tDCS (a-tDCS) vs. sham-tDCS (s-tDCS) in the tDCS-based study and AO+MI-BCI vs. AO-control AO+MI-based study, and the measurements times pre-treatment, post-treatment, and at 15 days post-treatment. If significant differences are found in any of the interactions, a post hoc analysis will be performed with Bonferroni correction. The effect sizes will be calculated by means of the d of Cohen, being classified as small (d between 0.20 and 0.49), medium (d between 0.50 and 0.79), or large (d greater than 0.80) following the method of Cohen.

For the rest of the psychological variables, a Pearson’s correlation with the physical variables will be carried out in order to find relationships between both. Low correlation will be taken as that with values between 0.2 and 0.39; the correlation will be considered moderate when the value goes from 0.40 to 0.79; and high when the value of the correlation is greater than 0.80.

For the analysis of neurophysiological variables rMT, MEP magnitudes will be determined by averaging peak-to peak amplitudes. The ratio of the rMT, MEP amplitude recorded at each post-intervention time-point relative to the baseline rMT will be calculated [(MEP amplitude at each stage–baseline MEP amplitude)/baseline MEP amplitude Å~100]. Statistical analyses will be performed on the calculated test-to baseline MEP ratios. For the CSP values the time will be measured manually in each trial and averaged and the ratio compared to baseline measurement will be also calculated.

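### The OFF-state measurements are meant to show the therapies' effect without dopaminergic medication, but the only analysis that names OFF tests whether the effect differs between ON and OFF

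*Protocol article*

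**What the plan says.** - **Purpose of the OFF data** (2.3 Outcomes Measurement). All outcomes are taken in ON. For three of them the section adds OFF: KPDPS is named first, then "CPM and TS will be also measured in OFF state, 30 min before medication intake". The reason given is "to assess the effects of both neuromodulation therapies when dopaminergic medication is not acting".
- **Analysis of the two-state data** (2.5 Data Analyses, last paragraph). A first part compares ON with OFF in pain intensity, CPM and TS. Then "the second part will investigate the effects of the intervention on these same variables comparing the differences between ON state versus OFF state". The method is repeated-measures ANOVA followed by Bonferroni post hoc tests, "using the interaction of group factor x state factor and time factor".
- **Analysis of the main variables** (2.5, first paragraph). Here "an analysis of variance (ANOVA) 2 × 3 of repeated measurements will be carried out taking time and group as factors". State is not a factor, and the text does not say whether ON values, OFF values or both enter. For this ANOVA, "If significant differences are found in any of the interactions, a post hoc analysis will be performed with Bonferroni correction".
- **Planning assumptions** (2.4.1, carried over to the second study in 2.4.2). The calculation was made "taking into consideration the design of two intervention groups and three assessment times", for "King’s Parkinson’s Disease Pain Scale with an estimated effect size of F = 0.25", at alpha 0.05 and 90% power. It gives 28 in total, raised to 32 (16 per arm) for 15% loss.

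**The concern.** The question in section 2.3 has a plain null hypothesis: in OFF, active and control do not differ in their change over time. The interaction named in section 2.5 has another null: the active-versus-control difference in change is the same in ON as in OFF. A therapy that helps in OFF and helps equally in ON satisfies the second null while violating the first. A therapy that helps in ON only violates the second while satisfying the first.

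So neither result of the named test answers the question for which the OFF assessments are made. A non-significant interaction could be reported as no OFF finding when there is a benefit, and a significant one could be taken as evidence of OFF benefit when there is none.

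**Working it through.** **1. What the interaction estimates.** Let D_ON and D_OFF be the active-minus-control differences in change from pre-treatment within each state. Then

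group x state x time = D_OFF − D_ON, whereas the question in section 2.3 concerns D_OFF alone.

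If D_OFF = D_ON, the interaction is exactly zero, whatever the size of the benefit and whatever the correlations.

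**2. The plan's own figure.** The usual power formula for a group x time interaction is lambda = f² × N × m / (1 − rho), with df1 = 2 and df2 = 2(N − 2). The article gives no rho. With f = 0.25, N = 28, m = 3 and rho = 0.5:

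lambda = 0.0625 × 28 × 3 / 0.5 = 10.5, power 81%.

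At rho = 0.5, 90% power needs N = 36. The stated 28 at 90% is obtained with rho of about 0.61 to 0.63. Since rho is not stated, this does not show the figure to be wrong, and the present point does not depend on it.

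**3. Effect size used.** For a constant shift d (in SD units) at both post-treatment visits, the interaction means are ±(d/2) × (−2/3, 1/3, 1/3). Hence f² = (d/2)² × 2/9. Setting f = 0.25 gives d = 2 × √(0.0625 / (2/9)) = 1.06 SD. Conversely, d = 1.0 gives f = 0.5 × √(2/9) = 0.24.

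**4. Simulation at f = 0.25.** 20,000 trials per scenario, two-sided alpha 0.05. Assumed, because the article gives no values: unit SD, correlation 0.5 between visits and 0.5 between states. The three-way test is group x time on OFF minus ON.

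| Shift in ON / OFF (SD) | Per arm | Group x state x time | Group x time, OFF only | Group x time, averaged over states |
|---|---|---|---|---|
| 1.06 / 1.06 | 16 | 5.1% | 86.6% | 94.8% |
| 1.06 / 1.06 | 14 | 4.8% | 81.3% | 90.9% |
| 1.06 / 0 | 16 | 86.5% | 4.8% | 39.8% |
| 0 / 1.06 | 16 | 86.6% | 86.7% | 38.8% |
| 0.53 / 1.06 | 16 | 29.8% | 86.6% | 75.0% |
| 1.06 / 0.53 | 16 | 30.5% | 30.9% | 74.6% |

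As a check, the formula in step 2 at rho = 0.5 gives 81.2% for N = 28 and 86.6% for N = 32, which agrees with the OFF-only column.

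**5. Sensitivity to the assumed correlations.**
- Equal effects, 16 per arm, ON-OFF correlation 0.3 to 0.9: the three-way test stays at 4.8 to 5.1%.
- OFF effect half the ON effect, same range: the three-way test runs from 23% to 94%.
- A separate simulation (3,000 runs per scenario, visit correlation 0.5, ON-OFF correlation 0.4 to 0.8) with 1.0 SD in both states gives about 5% against 81–83% with 16 per arm, and 4–6% against 77–78% with 14. With 0.5 SD in ON and 1.0 SD in OFF it gives 24–60% against about 82%.
- OFF-only effect: the variance of OFF minus ON is 2(1 − r) with r the ON-OFF correlation. At r = 0.5 this is 1, the same as for OFF alone, so the two tests tie. At higher r the three-way test is the stronger.

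**The case against.** **The three-way test is right for the question that section 2.5 sets itself.** Its second part compares ON with OFF, and the interaction tests exactly that. This stands, and it is why the interaction should be kept. It does not supply the analysis that section 2.3 calls for.

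**The wording is loose, and the interaction phrase may describe the post hoc tests.** Post hoc comparisons among the group, state and time cells would include active versus control in OFF. That is possible, but no such contrast is named. Reading the phrase as group x state would not isolate the OFF treatment effect either.

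**The 2 x 3 ANOVA could be run on OFF values.** KPDPS, CPM and TS are main outcomes, and nothing restricts that ANOVA to ON. This is fair as far as it goes. But the text does not assign OFF values to it, and the one paragraph that does deal with OFF uses a different model. A three-factor model also yields group x time, but that term averages over states. With an effect in ON only it rejects in 39.8% of trials although the OFF effect is zero.

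**Two stronger readings are tempting.**
- A reader might infer that an OFF benefit is bound to be missed, because post hoc tests are blocked when the interaction is not significant. That condition is written for the 2 x 3 ANOVA; the paragraph on ON and OFF does not repeat it.
- A reader might infer that equal benefit in both states is what the plan expects. The Introduction's hypothesis of superiority names no state, and the f = 0.25 in section 2.4.1 does not distinguish ON from OFF. The Introduction also says that reduced cortical excitability is seen especially in OFF, and section 2.2 places all sessions in ON, so state-dependent effects are quite possible. Equal benefit is one plausible case, not the stated one.

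**Conclusion.** The mismatch stands. The article gives a purpose for the OFF measurements, and the only analysis that names OFF answers another question. No sentence assigns an active-versus-control comparison to OFF values.

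The size depends on the pattern of effects. With equal benefit in both states, the named test rejects at about 5%, against about 81 to 87% for group x time on OFF values at f = 0.25 with 14 to 16 per arm. The 5% is algebraic; the 81 to 87% rests on the assumed correlation of 0.5 between visits. With a larger effect in OFF than in ON the loss is smaller, and with an OFF-only effect and ON-OFF correlation above about 0.5 there is no loss. In the opposite direction, an ON-only effect makes the interaction significant in about 87% of trials (16 per arm, ON-OFF correlation 0.5) with nothing happening in OFF.

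This should be corrected before analysis, but it is confined to the OFF-state question. The sample size in section 2.4 and the KPDPS superiority criterion in section 2.6 do not rest on this interaction.

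**What to change.** In the last paragraph of section 2.5, state that:

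1. the effect of each therapy in OFF is tested by the active-versus-control (group x time) comparison on the OFF values of KPDPS, CPM and TS, reported with 95% CIs;
2. these comparisons are secondary and are made whether or not the three-way interaction is significant;
3. the group x state x time interaction is kept as the test of whether the effect differs between ON and OFF, and is not read as evidence for or against an effect in OFF.

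The cost is a change of wording and one extra model per OFF outcome, on data already to be collected. The downside is three further secondary tests in each study (with one summary measure per outcome), to be labelled as such.
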